## Abstract

Aims: Atrial fibrillation (AF) is the most common sustained cardiac arrhythmia and a key risk factor for ischaemic stroke. Following AF detection, treatment with oral anticoagulation can significantly lower mortality and morbidity rates associated with this risk. The availability of several hand-held devices which can detect AF may enable trained health professionals to adopt AF screening approaches which do not interfere with people’s daily routines. This study aims to investigate the effectiveness of a hand-held device (the MyDiagnostick single-lead Electrocardiogram (ECG) sensor) in screening for AF when embedded into the handles of supermarket trolleys. Methods: A mixed methods two-phase approach will be taken. The quantitative first phase will involve the recruitment of 2000 participants from a convenience sample at four large supermarkets with pharmacies. Prospective participants will be asked to conduct their shopping using a trolley embedded with a MyDiagnostick sensor. If the device identifies a participant with AF, the in-store pharmacist will be dispatched to take a manual pulse measurement and a static control sensor reading and offer a cardiologist consultation referral. When the sensor does not detect AF, a researcher will confirm the reading with a manual pulse measurement. ECGs will be compiled, and the sensitivity, specificity and positive and negative predictive values will be determined. A qualitative second phase will consist of semi-structured interviews carried out with those pharmacists and store managers in-store during the running of the trial period. These will explore the perceptions of staff regarding the merits of embedding sensors in the handles of supermarket trolleys to detect AF. Conclusion: This feasibility study will inform a larger future definitive trial.

## 1. Introduction 

Cardiovascular disease accounts for almost a quarter (24.7%) of all premature deaths in men and nearly a fifth (17%) in women in the U.K. [1]. Four percent of these deaths are stroke-related [1]. Indeed, while stroke mortality rates have reduced over time, the condition remains one of the major global causes of mortality and disability [2]. In the U.K., stroke is the third most common cause of years of life lost and of disability [3] and is estimated to cost the UK Health and Social Care system GBP 8.6 billion per annum [4]. This cost equates to GBP 22,429 in the first year, with ongoing five-year costs of GBP 46,039 per patient [2]. Eighty-seven percent of these admissions (126,640) are ischaemic stroke-related, and atrial fibrillation (AF) is responsible for around a quarter of such strokes, which are more likely to be severe and fatal compared to other causes of stroke [5,6]. Unlike many other cardiac conditions, recent UK registry-based data has noted that the prevalence of AF is increasing [1], which, if not treated effectively, will likely result in an increasing number of strokes in the longer term, with a major impact on NHS healthcare costs related to AF [7]. Moreover, Public Health England estimates that while around 123,000 people in England are living with AF, around 20% of these people are undiagnosed and are therefore untreated [8].

Whilst it is recognised that the risk of stroke in patients with AF is not homogeneous, all patients with AF should be risk-assessed using the CHA_2_DS_2_-VASc score [9,10], with most patients, except the very lowest risk (CHA_2_DS_2_-VASc score of 0 in men and 1 in women), receiving oral anticoagulation therapy. Anticoagulant therapy, using either vitamin K antagonists (VKAs) or non-vitamin K antagonist oral anticoagulants (NOACS), markedly reduces the risks of stroke and mortality in AF patients [11,12]. More recent focus has been placed on the detection and characterisation of AF patients, followed by a holistic approach to AF care, given the improved clinical outcomes with integrated care management [13,14].

The detection and diagnosis of AF requires ECG rhythm documentation showing the typical pattern of irregular RR intervals with an absence of discernible P waves [10]. By accepted convention, an episode lasting at least 30 s is considered diagnostic [10]. However, whilst an ECG provides documentary evidence, the presence of an irregular pulse arouses suspicion of AF and whilst not as specific or as sensitive as the ECG, checking an individual’s pulse is much less costly and requires fewer resources. A pulse check is therefore an easy, low cost means of ruling out or raising suspicion of AF, as an approach to AF screening [15].

However, the regularity of a person’s pulse and the normality of their ECG are usually only confirmed as a result of either opportunistic screening [10] or post-event identification. Silent or undetected AF is not uncommon [16,17], and although opportunistic screening is considered cost-effective in some populations [18], it may be seen as an inconvenience to those not currently experiencing symptoms and may be irrelevant to some socioeconomically deprived groups who do not engage with health professionals until a crisis occurs. Therefore, alternative models of screening that can be delivered by appropriately qualified personnel whilst not detracting people from their daily activities are required. Until recently, such a process has been impractical; however, with the advent of new technology, this may now be possible, as a number of validated hand-held devices are available that allow irregular pulses to be detected.

MyDiagnostick is a cylindrical shaped MDD Class IIa medical device (length 26 cm, diameter 2 cm) costing circa GBP 550 that records a single lead I ECG tracing when a participant’s hands make contact with the metal electrodes (Figure 1). The device’s algorithm-based internal software analyses the R-R interval of the ECG recording over a one-minute period whilst contact is maintained. The presence of AF is signified by a red light (Figure 2), whereas the absence of AF is signified by a green light (Figure 3). A single lead tracing can then be downloaded via a USB port onto a computer as a PDF document for further analysis. Whilst the MyDiagnostick algorithm is focussed solely on the presence or absence of AF, the PDF generated allows a trained professional to identify additional arrhythmias if present.

We propose to embed a MyDiagnostick single lead ECG sensor into the handles of supermarket trolleys to assess the person’s heart rhythm whilst they undertake their shopping (Figure 1). If an abnormal heart rhythm is detected, the store’s pharmacist is notified and is dispatched to meet with the shopper. Community-based pharmacies have been identified as a potential location to undertake opportunistic screening and lifestyle interventions [19]. Previous studies have demonstrated that pharmacists are able to successfully screen and identify those at risk of cardiovascular disease [20,21] and is acceptable to patients [22], but again, these studies have relied on self-presentation.

## 2. Methods

We are proposing to locate a research team in four large supermarkets that contain pharmacies where shoppers will be asked to test the embedded technology, and store managers and pharmacists will provide their views on the merits of the screening approach. We will do this using a mixed methods two-phase approach.

### 2.1. Phase 1

#### 2.1.1. Study Design

A cross-sectional observational study with a convenience sample will be used to address the research objectives.

#### 2.1.2. Eligibility Criteria

Members of the public who are visiting four large supermarkets in the North West of England. We will recruit from four supermarkets for a period of two months each. To be eligible for inclusion, participants must be aged ≥18 years, able to grip a shopping trolley handle and provide written informed consent. Participants will be excluded if they have a physical tremor as this affects the ability of the device to record the heart rhythm due to movement artefact and previously participated in the study. Those with known AF will not be excluded from participation as the inclusion of this group of patients will aid the assessment of the sensitivity of the sensor and minimise selection bias.

#### 2.1.3. Sample Size

Large supermarkets attract an average footfall of 25,000 people per week [23], providing a potential total population across four stores per week of 100,000 people. Recognising that many of these people are returning customers attending on a weekly basis, this study aims to recruit around 2% of the total population, resulting in a sample of 2000 participants. The prevalence of AF in the area of the North West of England from which participants are to be recruited is estimated to be 2.1% [24,25], which would result in 42/2000 positive results, including some who are known to experience AF. However, we recognise that those most at risk of developing AF are ≥ 65 years. Unfortunately, neither the British Retail Consortium nor YouGov provides age-related data for in-store supermarket shopping. One American study estimated that those over the age of 60 years make up 24% of supermarket consumers [26]. Recognising that the prevalence of AF is highest in this older age group, ranging from 4–11% in those 65–79 years old, we estimate a total of 480/2000 people will be screened from within this age group and between 19/480 and 53/480 people will be found to be in AF. In addition, it is estimated that the remaining 1520 customers present between 0.1–1.5% risk of AF suggesting between 2/1520 and 23/1520 additional presentations. In total, it is estimated that between 21 and 76 participants will be found to be suffering AF [27]. The prevalence of undiagnosed AF differs dependent on age. A systematic review of 30 single time-point AF screening studies including 122,571 participants (Lowres et al., 2013) reported the incidence of previously unknown AF as 1.0% (CI, 0.89–1.04%), increasing to 1.4% (CI, 1.2–1.6%) in those >65 years old. We recognise that we are recruiting a yonger population than those included in these studies, we therefore estimate that up to 28 people will be identified with undiagnosed AF.

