#### 2.1.9. Statistical Analysis

A sensitivity of 95% and specificity of 90% is sufficiently accurate to be incorporated into clinical practice. If confirmed, they will make supermarkets with in-store pharmacies a nationwide relevant and cost-effective point of screening AF. Such high sensitivity and specificity values are also indicated as plausible by existing published papers, with 95% confidence intervals of 93–100% and 91.3–98.1% [29] and 87–98% and 85–97% [28], for sensitivity and specificity, respectively. In our proposed feasibility study, our precision calculations show that with between 21 and 76 AF cases, we will estimate the 95% confidence interval of sensitivity and specificity with interval widths of 19.0% and 9.8%. The most likely precision will be 12.4%.

Descriptive statistics including simple percentages will be estimated from this feasibility study to demonstrate uptake, rates of detection and successful referral. Generating these data will enable the researchers to determine the number of shoppers who need to be approached to recruit for an adequately powered future study. In addition, conditional percentages will be used to describe the sensitivity and specificity of both the sensor and the pulse check.

By recruiting from community supermarkets based in areas of high deprivation, it is likely that we will recruit a greater number of individuals who are known not to typically engage in traditional screening programmes. This approach attempts to correct the inverse care law, bringing healthcare to the community.

### 2.2. Phase 2

The second phase of the study involves an embedded qualitative approach. The primary objective is to explore the views of supermarket-based pharmacists and store managers on the merits of embedding pulse sensors in the handles of supermarket trolleys to enable the detection of AF. The secondary objective is to explore the pharmacists’ perspectives and experiences of performing manual pulse checks on participants.

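### The expected AF case count and the sensitivity precision assume, without saying so, that everyone with AF is in AF during the shopping visit

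*Protocol article*

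**What the plan says.** Section 2.1.3 (Sample Size) reaches its case count by two routes. The area prevalence of 2.1% is applied to all 2000 participants, "which would result in 42/2000 positive results, including some who are known to experience AF". Separately, 480 older shoppers are given a prevalence "ranging from 4–11% in those 65–79 years old", so that "between 19/480 and 53/480 people will be found to be in AF", and the other 1520 are given a risk of 0.1-1.5%, which adds 2 to 23. The total is 21 to 76.

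Section 2.1.9 (Statistical Analysis) carries the range forward unchanged: "with between 21 and 76 AF cases, we will estimate the 95% confidence interval of sensitivity and specificity", with widths of 19.0% and 9.8% and a most likely value of 12.4%.

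The Introduction says the device "analyses the R-R interval of the ECG recording over a one-minute period whilst contact is maintained". Section 2.1.7 adds that the handle is held at different times and for different lengths during one shopping trip, and that each contact is recorded.

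For undiagnosed AF only, section 2.1.3 uses single time-point screening data (1.0%, rising to 1.4% in those over 65) and expects up to 28 people.

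**The concern.** A prevalence of AF that includes known AF normally counts people who have the condition. The number who can give a true positive is the number in AF while holding the handle. The two are equal only if nobody with AF is in normal rhythm during the visit. The article neither states nor defends that assumption, and its own diagnostic convention in the Introduction is framed in terms of episodes.

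The count matters because the sensitivity estimate rests on the shoppers in AF when recorded. If fewer are in AF than planned, the interval is wider than section 2.1.9 says. Specificity is hardly touched, since it rests on nearly 2000 non-cases. The point is separate from false alarms: it would apply with a perfect sensor.

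**Working it through.** **Inputs from the documents.** 2000 participants, 2.1% prevalence, the age-band figures, up to 28 undiagnosed (section 2.1.3); sensitivity 95% and the stated widths (section 2.1.9); about 20% of AF undiagnosed (Introduction).

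**Input not in the documents.** f, the share of known AF in normal rhythm during the visit. Assumed range: 0.2 to 0.5.

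**Step 1: reproduce the plan's counts.**
- 2000 × 0.021 = 42.
- Low: 480 × 0.04 + 1520 × 0.001 = 19.2 + 1.5 = 20.7, or 21.
- High: 480 × 0.11 + 1520 × 0.015 = 52.8 + 22.8 = 75.6, or 76.

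**Step 2: reproduce the widths.** Normal-approximation 95% width = 2 × 1.96 × √(0.95 × 0.05 / cases).
- 21 cases: 18.6 points (the stated 19.0 corresponds to about 20.2 cases).
- 76 cases: 9.8 points, as stated.
- 42 cases: 13.2 points.
- The stated 12.4 corresponds to about 47.5 cases.

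The plan's figures therefore reproduce, to within rounding of the case count at the low end, with every prevalent case counted as in AF at the visit (f = 0).

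**Step 3: allow for known AF in normal rhythm.** Cases in AF at the visit = undiagnosed + known × (1 − f). The undiagnosed part is not reduced, because the plan takes it from single time-point screening. The documents support two different splits:
- Split A: 28 undiagnosed (the upper figure in section 2.1.3), the rest known.
- Split B: 20% undiagnosed and 80% known (Introduction), giving N × (1 − 0.8f).

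For N = 42, split A gives 28 + 14 × 0.8 = 39.2 and 28 + 14 × 0.5 = 35. Split B gives 42 × 0.84 = 35.3 and 42 × 0.60 = 25.2.

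| Planned cases (width) | Split A, f = 0.2 to 0.5 | Split B, f = 0.2 to 0.5 |
|---|---|---|
| 21 (18.6) | not applicable: 28 exceeds 21 | 17.6 to 12.6 cases; 20.3 to 24.1 points |
| 42 (13.2) | 39.2 to 35 cases; 13.6 to 14.4 points | 35.3 to 25.2 cases; 14.4 to 17.0 points |
| 47.5 (12.4) | 43.6 to 37.8 cases; 12.9 to 13.9 points | 39.9 to 28.5 cases; 13.5 to 16.0 points |
| 76 (9.8) | 66.4 to 52 cases; 10.5 to 11.8 points | 63.8 to 45.6 cases; 10.7 to 12.7 points |

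**Step 4: a reading that removes the shortfall.** If the 2.1% counted diagnosed AF only, the undiagnosed would be additional: from 42 × 0.5 + 20 = 41 to 42 × 0.8 + 28 = 61.6, where 20 and 28 are 1.0% and 1.4% of 2000. The planned 42 would then not be overstated to any extent that matters.

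**The case against.** The strongest reply is that neither size nor direction can be fixed from the article. No share of intermittent AF is given. If a cited prevalence came from point-in-time ECGs, that component needs no reduction; if it counted diagnosed AF only, step 4 applies. The words about including some known cases lean against the diagnosed-only reading but do not settle it. This stands, and it is why the point is an unstated assumption rather than a proven overstatement.

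It can also be said that little in the design follows from the count. The 2000 comes from about 2% of weekly footfall, the reduced central counts of 25 to 39 remain within 21 to 76, and the future study is to be planned from observed uptake, detection and referral. That is right, and it limits the consequence to the stated precision.

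Two stronger readings are tempting, and the documents support neither:
- A reader might infer that a known-AF shopper with a correct green light would be scored as a miss. No section makes AF history the reference. Section 2.1.7 sets a manual pulse check after a negative reading, and a repeat sensor and pulse check after a positive one. Section 2.1.8 compares 12-lead ECGs of referred participants with the sensor recordings.
- A reader might infer that section 2.1.2 is wrong to say that "the inclusion of this group of patients will aid the assessment of the sensitivity of the sensor". Known-AF shoppers who are in AF at the visit do add to the sensitivity denominator, so the statement holds for them.

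**Conclusion.** The concern holds as an unstated planning assumption. The counts of 42 and 21-76, and the sensitivity widths drawn from them, require every prevalent case to be in AF during the visit, and the article makes no allowance for any who are not.

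With 20-50% of known cases in normal rhythm, the effect on the central count runs from small (about 39 cases, 13.6 points) to material (about 25 cases, 17.0 points), depending mainly on how many cases are already known. The low end is the most exposed: with 80% known, its width of 20.3-24.1 points passes the stated maximum of 19.0. These sizes rest on the assumed f, on the choice between two splits that the article itself does not reconcile, and on the prevalences being counts of people with the condition, diagnosed or not. They are not a finding that the counts are wrong by a known amount.

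**What to change.** - In section 2.1.3, say for each prevalence (2.1%, 4-11%, 0.1-1.5%) whether it is a point-in-time figure and whether it covers diagnosed AF only.
- Where a figure is not point-in-time, split it into known and undiagnosed parts. Multiply the known part by a stated range for the proportion in AF at the visit, for example 50-80% (the complement of the f used here), with a source or marked as an assumption. Keep the single time-point screening rate for the undiagnosed part.
- Restate the expected cases and carry them into the sensitivity widths in section 2.1.9.

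This is rewording and recalculation, with no extra participants or procedures. The downside is a smaller stated case count and a wider stated interval, unless the sources prove to be point-in-time or diagnosed-only.

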#### 2.1.4. Recruitment

A convenience sample of all those attending four designated supermarkets in the North West of England. We will station a researcher at the entrance of each store who will approach shoppers as they enter the store and invite them to participate in the study. Participant information sheets on the trolley will outline the study and provide details of how people can participate and also include details of the funder (Bristol Myers Squibb). The supermarkets included in the study are located within the Liverpool City Region, a region with pockets of high levels of deprivation. The supermarkets are situated within community hubs and recognise their social responsibility.

#### 2.1.5. Informed Consent

Verbal consent will be gained prior to recruitment, with written consent obtained for all participants with an abnormal sensor reading whose personal data are required for onward referral to a consultant cardiologist.

#### 2.1.6. Sensor Technology

The sensor used within this study, MyDiagnostick has been shown to be highly sensitive in detecting AF, with sensitivity levels ranging between 94% (95% CI 87–98%) [28] to 100% (95% CI 93–100%) [29]. The specificity of MyDiagnostick also compares well with other devices ranging between 93% (95% CI 85–97%) [28] to 95.9% (95% CI 91.3% to 98.1%) [29].

#### 2.1.7. Study Procedures

We will recruit 2000 people attending one of four supermarkets in the North West of England. Each participant will use a supermarket trolley to undertake his or her routine shopping and, by doing so, will grip the trolley handle at differing points and for differing time periods. It will be made clear to each participant that only one person should push the trolley during his or her visit to the store. During each contact with the trolley handle, the sensor will assess the participant’s pulse and store a recording of the rhythm strip, which is stored within the sensor’s file storage system. These data will be downloaded alongside the personal data at the end of each day and deleted from the storage system. The handles of all trolleys will be sanitised between participants to minimise the risk of infection.

If the pulse sensor detects AF, the store pharmacist will be alerted by the researcher, and they will meet with the participant in the store to repeat the sensor check and undertake a manual pulse check. If the pulse sensor does not detect AF whilst the person is pushing the trolley, the researcher will meet with the participant and a manual pulse check will be undertaken once the person has completed their shopping. The procedure to be followed for each participant is outlined in Figure 4. An irregular pulse is defined as any irregularity between pulse waveforms in the radial artery within a period of sixty seconds. Guidance recommends pulse palpation as the first step for AF screening [10]. Two randomised controlled trials have found that pulse palpation is an effective and cost-effective approach for screening for AF [18,30]. All staff undertaking manual pulse checks will undertake additional training using simulation manikins to ensure that they are practising in line with the procedures outlined in the Royal Marsden Manual of Clinical Nursing Procedures [31]. However, a static sensor check (control) will provide an ability to differentiate between normal irregular pulses, e.g., sinus arrhythmia and more harmful conditions, including AF.

With consent, details of all those who are found to have an irregular sensor reading will be stored on a research database. A Consultant Cardiologist will review the sensor recordings to eliminate those recordings that are uninterpretable and whereby the sensor has been activated by the presence of the artefact. These participants will be invited to return for an additional static check. The details of those with confirmed AF or suspected AF will be referred to a local healthcare facility. These details will be compared against those who attend a follow-up ECG. Anyone who has not attended an ECG assessment will be contacted by telephone within one week of referral. During this telephone call, the participant will again be made aware of the risks associated with an irregular pulse, and a further invitation to attend a clinic for an ECG will be offered. Participants who do not attend will be contacted on two occasions, after which, if they still have not attended, a letter will be sent to their GP explaining that the detection of an irregular pulse was found during a screening study. Follow-up care will then be provided by the GP as per routine NHS care. All data will be aggregated, enabling comparisons to be made. As the aim of the study is to assess the merit of the screening approach, the study follow-up will discontinue once the participant has attended the cardiology clinic or failed to attend despite two follow-up telephone calls. All treatment beyond this stage will be in line with contemporary NHS AF pathways, and consequently, the likely incidence of stroke will be extrapolated from the results of national datasets.

